### *Assessing Outcomes*

*Implementation outcomes.* This is a hybrid Type II effectiveness implementation trial. Thus, we are interested in the implementation of the LHS intervention. We will assess implementation with self-report surveys, qualitative interviews, and focus groups. We will also include the Stages of Implementation Completion (SIC) measure, an 8-staged observation-based assessment tool created as part of a large-scale randomized implementation trial comparing two implementation processes. The SIC stages - which we will apply throughout the study period to measure implementation outcomes - range from: Engagement with the academic team to achievement of practitioner Competency and map onto three well-accepted phases of implementation (Pre-Implementation (i.e., exploration and planning), Implementation, Sustainability). The SIC has demonstrated valid and reliable measurement of implementation activities, specifically the proportion and duration of implementation activity completion. Lastly, we will complete three sets of qualitative and focus group interviews. By utilizing a mixed method approach, will be triangulate results and gather a more nuanced picture of implementation issues.

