*Step 2.* The analyses will be similar to that described above in Step 1 except the implementation variables (readiness, climate support, leadership support, and collaborative alliance) will be used as independent variables to predict the dependent variable of implementation fidelity. Fidelity will be measured (in three separate models) using the SIC Pre-implementation score, the SIC Implementation score, and the SIC Sustainability score. In exploratory analyses, two additional fidelity dependent variables will be analyzed: percentage of activities performed, and Duration (number of days between activities). The analysis for Aim 4 describes how implementation climate and fidelity measures will be used in models as predictors of the SU cascade of care and opioid related outcomes.

*Aim 3 Power.* We require a total sample size of 384 enrolled (we will be conservative and enroll 395) JJ and CMHC staff for the implementation surveys. The actual analysis will employ linear mixed models that incorporate all staff participants with available implementation outcomes variables collected at multiple survey time points (Study Month 8, 14, 20, 26, 32, 38). The analysis models will actually also account for a second clustering variable (i.e., within each county, we will have surveys from staff of one

JJ system, and surveys from staff of one CMHC system), yielding 16 total clusters (8 counties by two JJ/CMHC sites within each county). However, the sample size inflation factor is greater with fewer clusters; therefore, for power calculations, we conservatively assumed 8 clusters instead of 16 total clusters. We used the PASS software to calculate power for a test comparing two means (control condition mean vs treatment condition mean) in a cluster-randomized step wedge design. Our step wedge design is an “incomplete design” in which a different number of clusters (i.e., counties) start the intervention at each step. Additional detail about the step wedge design, including clusters, cohorts, steps, timeline and design matrix, is provided below under the power section for Aim 4. Unlike Aim 4 which will have extensive (conservatively 6 months, actually 5 years) prior baseline administrative data for the control condition, the implementation scale data for Aim 3 is collected at a single baseline point (study month 8) and this will be used as the control condition measurement.

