climate support, leadership support, and collaborative alliance), and fidelity variables (SIC Pre-implementation, Implementation score, and Sustainability scores; percentage of activities performed; and number of days between activities) to determine whether these survey variables predict the response rates for the SU cascade and opioid related outcomes. The implementation and fidelity measures will be entered as time-varying predictors because they will be available from multiple survey measurement time points as described above for the analysis of Aim 3.

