However, we acknowledge some youth will be placed out of the home (DOC and residential placement). Additionally, some youth will migrate out of the community (which will be assessed by address data from state-wide databases; INPC, Medicaid, & DCS). Thus, we conservatively estimate that roughly 70% of 2,170 (i.e., 1,519) adolescent arrestees per year will be available in-home in the community from the 8 counties (4,557 total over 36 months of implementation which includes 30 months of intervention plus 6 prior months in which all cohorts experience the control condition under the baseline period). Based on an annual 30% recidivism rate, we estimate that 30% (1,367) of the projected 4,557 arrests for this trial will represent repeated arrests from the same youth, yielding an estimated 3,190 unique youth available in the administrative data over the 36 months of the primary outcome measurement period. We will actually collect and use administrative data for 5 years (not just 6 months) prior to the start of intervention; however, to be conservative, the step wedge power calculation assumed only 6 months of prior baseline administrative data (i.e., 36 months of primary administrative measurement). Additionally, although all data (including multiple arrests for the same youth) will be used in the model, to be conservative for the power analysis, we assumed that the maximum sample size available for the power calculations is the number of unique youth (3,190).

Our design has 8 counties (i.e., clusters). A projected maximum available sample size of 3,190 unique youth, over the 36-month primary evaluation period, yields: (1) 531 youth per 6-month time period, (2) an average of 398 maximum youth per cluster over 36 months (*M* in the Step Wedge Design), and (3) an average of 66 youth per cluster per 6-month time period (*m* in Step Wedge design).

We used the PASS software to calculate power for a test of two poisson rates (control condition event rate vs treatment condition event rate) in a cluster-randomized step wedge design. Our step wedge design is an "incomplete design" in which a different number of clusters (i.e., counties) start the intervention at each step. Given 8 clusters and practical considerations, we decided to initiate intervention for 3 clusters in cohort 1, then in the next step another 3 clusters in cohort 2, and then in the next step another 2 clusters in cohort 3.

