We input the following customized design matrix into the PASS software. The timeline, shown elsewhere in this application, is displayed in 3-month increments to show specific details such as the 3 months of dissemination at the end of study. For the step wedge design matrix, each time period

represents a 6-month time interval because the administrative outcome data will be measured every 6 months, and the cohorts will also be started on intervention in 6-month steps of our step wedge design.

Step Wedge Design Matrix (Incomplete Design: K = 8 Clusters, S = 5 Steps, T = 6 Times Periods)

|        |                | Time (6-month intervals) |        |         |          |          |          |
|--------|----------------|--------------------------|--------|---------|----------|----------|----------|
|        |                | 1                        | 2      | 3       | 4        | 5        | 6        |
|        |                | Intervention Months      |        |         |          |          |          |
| Cohort | County Cluster | -6 to 0                  | 1 to 6 | 7 to 12 | 13 to 18 | 19 to 24 | 25 to 30 |
| 1      | 1              | 0                        | 1      | 1       | 1        | 1        | 1        |
| 1      | 2              | 0                        | 1      | 1       | 1        | 1        | 1        |
| 1      | 3              | 0                        | 1      | 1       | 1        | 1        | 1        |
| 2      | 4              | 0                        | 0      | 1       | 1        | 1        | 1        |
| 2      | 5              | 0                        | 0      | 1       | 1        | 1        | 1        |
| 2      | 6              | 0                        | 0      | 1       | 1        | 1        | 1        |
| 3      | 7              | 0                        | 0      | 0       | 1        | 1        | 1        |
| 3      | 8              | 0                        | 0      | 0       | 1        | 1        | 1        |

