#### *Missing Data*

For analyses of all aims, bias due to missing data will be handled by using the state-of-the-art multiple imputation method with 100 multiply include data sets using the SAS MI and MIANALYZE procedures.

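### Aim 3 Step 2 models SIC Implementation and Sustainability scores across waves that include pre-LHS periods, with no LHS term listed; if those periods score zero, collaboration is confounded with LHS status

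*Protocol*

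**What the plan says.** Under Assessing Outcomes, the protocol describes the SIC as an eight-stage, observation-based tool whose stages map onto Pre-Implementation, Implementation and Sustainability phases, "which we will apply throughout the study period to measure implementation outcomes". It says that the tool measures the proportion and duration of completed activities.

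Aim 3 Step 2 makes the three phase scores the outcomes: "Fidelity will be measured (in three separate models) using the SIC Pre-implementation score, the SIC Implementation score, and the SIC Sustainability score". The predictors are readiness, climate support, leadership support and collaborative alliance. On model form it says "The analyses will be similar to that described above in Step 1". Step 1 uses linear mixed models over six waves (study months 8, 14, 20, 26, 32, 38). Its listed independent variables are Time and staff survey covariates. It lists no indicator for whether a county is on LHS.

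Aim 4 uses the same scores again, as predictors added in a later step: "The implementation and fidelity measures will be entered as time-varying predictors because they will be available from multiple survey measurement time points". The Missing Data section applies to everything: "For analyses of all aims, bias due to missing data will be handled by using the state-of-the-art multiple imputation method".

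No section says what value an Implementation or Sustainability score takes before a county has started LHS, and none limits Step 2 to counties on LHS.

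**The concern.** A county still waiting for LHS has nothing to implement or sustain. For a measure of activity completion, the natural value in that period is zero. A zero-scored phase score then jumps when the county starts LHS, whatever the quality of its collaboration. Alliance, readiness and climate are expected to rise at the same moment, because that is the hypothesis of Aim 3. With no LHS term in the model, both sides of the regression carry the same on/off signal, and the model reads it as alliance predicting fidelity.

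At stake is the interpretation of Step 2. A trial in which LHS succeeds in raising alliance would be likely also to report that better alliance drives better implementation, even if better-allied counties implement no better than the others.

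**Working it through.** **Inputs.** The design is "Incomplete Design: K = 8 Clusters, S = 5 Steps, T = 6 Times Periods" (Aim 4 Power, which Aim 3 Power cites for its own design). For roll-out, "we decided to initiate intervention for 3 clusters in cohort 1, then in the next step another 3 clusters in cohort 2". Cohort 3, the remaining 2 counties, starts one step later. From Aim 3 Power: ICC 0.01, SD 1.00, two-sided alpha 0.05, m = 8 respondents per cluster-period, smallest effect d = 0.56. Assumed, because the protocol gives no figures: SIC phase score under LHS with mean 0.7 and SD 0.15, or mean 0.6 and SD 0.18, and unrelated to alliance.

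**Pre-LHS county-periods.** 3 counties x 1 + 3 x 2 + 2 x 3 = 15 of 8 x 6 = 48 (31%): 8, 5 and 2 in periods 1, 2 and 3. On LHS: 48 - 15 = 33. This aligns the six survey waves with the six design periods.

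**The plan's own figure.** The Hussey-Hughes variance is K s2 (s2 + T t2) / [(KU - W) s2 + (U^2 + KTU - TW - KV) t2].
- s2 = 0.99/8 = 0.12375; t2 = 0.01.
- U = 33; W = 3^2 + 6^2 + 3 x 8^2 = 237; V = 3 x 25 + 3 x 16 + 2 x 9 = 141.
- KU - W = 264 - 237 = 27; U^2 + KTU - TW - KV = 1089 + 1584 - 1422 - 1128 = 123.
- Variance = 8 x 0.12375 x 0.18375 / (27 x 0.12375 + 123 x 0.01) = 0.1819/4.571 = 0.0398; SE = 0.1995.
- Power at d = 0.56 = Phi(0.56/0.1995 - 1.96) = 0.80, as stated. The values for 0.60, 0.70 and 0.80 also reproduce (0.853, 0.939, 0.980). So the matrix is the one behind Aim 3.

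**Expected false slope when pre-LHS cells score zero** (period effects plus alliance, no LHS term, true link zero):
- Sum of squares of the LHS indicator within periods = 27/8 = 3.375.
- Cross-product of score and alliance = d x SIC mean x 3.375 = 0.56 x 0.7 x 3.375 = 1.323.
- Alliance sum of squares = 0.56^2 x 3.375 + (0.01 + 0.12375) x 42 = 1.058 + 5.618 = 6.676.
- Slope = 1.323/6.676 = 0.198; simulated mean 0.198.
- At d = 0 the cross-product is zero, so no false slope arises.
- More respondents per cell shrink the noise term, so the false slope grows.

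**Simulated false-positive rate** (nominal 5%; county-period regressions with period effects, SIC mean 0.7 and SD 0.15, 8 respondents per cell; the two figures are without / with county effects):

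| LHS effect on alliance | Zero-scored, no LHS term | Zero-scored, LHS term added | 33 on-LHS cells only |
|---|---|---|---|
| 0 | 4.7% / 4.3% | 4.3% / 4.6% | 4.4% / 4.9% |
| 0.28 | 22.6% / 17.4% | 4.5% / 4.8% | 4.5% / 4.7% |
| 0.56 | 61.7% / 50.6% | 5.4% / 5.3% | 5.1% / 4.8% |
| 0.80 | 90.7% / 79.9% | 5.3% / 5.1% | 5.7% / 5.9% |

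With SIC mean 0.6, SD 0.18, county and period effects and d = 0.56, the rate is about 40% with 8 respondents per cell, 81% with 24 and 98% with 49. Forty-nine is 395/8, which reads Step 1 as surveying all 395 staff at every wave.

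**Imputation.** When the 15 cells were imputed from the on-LHS cells, rejection was 3.5-5.5% and the mean slope near zero.

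**The case against.** The strongest reply is that zero-scoring is not in the protocol. Handling of not-yet-applicable scores is the kind of detail a SAP can settle, and the SAP is not at hand. Step 1 also opens by invoking standard stepped-wedge methods to compare control with intervention, and such models normally carry a condition term; with one, the false-positive rate is about 5% even with zeros kept. The Outcome Measures table adds that SIC results will be evaluated at completion of the intervention period, when every county is on LHS.

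Part of this stands. Zero is an inference from the phase names and from the description of the SIC as a measure of activity completion. But the protocol itself fixes the outcomes, the predictors, the six waves and the listed terms, and that list omits LHS status. The end-of-period evaluation is additional to continuous measurement, and Aim 4 treats the scores as time-varying.

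Four stronger readings are tempting and not supported:
- **That imputation also manufactures a link.** It did not in the check above. The objection to it is one of meaning: it fills in fidelity to something that has not begun. The Missing Data section does not say that such scores count as missing.
- **That all three SIC scores are affected.** Pre-implementation activity can precede LHS start, so that score is not affected in the same way.
- **That the Aim 4 LHS estimate is compromised.** Aim 4 sets out the control-versus-LHS model first and adds SIC in a next step. A zero-scored SIC overlaps heavily with the LHS term, but only in that later step.
- **That a false result is near certain.** Rates near 98% need about 49 respondents per cell as well as d = 0.56.

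**Conclusion.** The point holds for the Implementation and Sustainability models of Aim 3 Step 2. As listed, these models cannot separate alliance from LHS status if pre-LHS cells score zero. At the protocol's own d = 0.56 with no true link, the false-positive rate is about 40-62% with 8 respondents per county-period and up to about 98% with 49.

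This rests on three conditions: pre-LHS cells scored zero, LHS raising alliance, and no LHS term in the fitted model. Remove any one and the rate is near 5%. The SIC mean and SD are assumed and change the size of the effect, not its direction. The simulations use county-period regressions with alliance as the only implementation predictor, which is simpler than the planned mixed model.

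The count of 15 is a minimum for Sustainability, which may also be undefined early in LHS. Aim 3 Power calls only the month 8 survey the control measurement, which on its own would give 8 of 48; the matrix gives 15.

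Step 2 is a secondary association analysis. It sets no sample size and does not produce the main effectiveness estimate, but the bias is large and easily avoided.

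**What to change.** - **Aim 3, Step 2:** state how Implementation and Sustainability scores are handled before LHS start. Then either fit those two models only on county-periods after that county's LHS start, or keep all periods and add an LHS indicator. Either restores about 5%.
- **Missing Data:** exclude from multiple imputation any SIC score that does not yet apply.
- **Aim 4 Analyses:** state that the LHS effect is taken from the first-step model, before SIC enters, and that the LHS coefficient from the later SIC step is not interpreted.

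The cost is wording plus a modest loss of information: Step 2 uses 33 county-periods instead of 48 (fewer for Sustainability if it starts later), or spends one degree of freedom on the LHS term. No data collection changes.

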### Report Definitions

S is the number of steps in the study design.  $S = T - 1$ .

T is the number of time periods in the study, including the baseline.  $T = S + 1$

R is the number of times that each row of the custom design pattern matrix is replicated.

K is the total number of clusters to be randomized.

M is the average number of subjects per cluster.

m is the average number of subjects per cluster per time period.

N is total sample size from all clusters and time periods combined.

$\mu_1$  is the treatment mean, assuming the alternative hypothesis.

$\mu_2$  is the control, standard, reference, or baseline mean.

$D1 = \mu_1 - \mu_2$  is the difference assuming the alternative hypothesis ( $H_1$ ).

$\sigma$  is the subject-to-subject standard deviation.

ICC is the intra-cluster correlation coefficient.

### Summary Statements

A sample of 8 clusters in an incomplete (or custom) stepped-wedge cluster-randomized design with 6 time periods (including the baseline), 5 steps, and an average of 48 subjects per cluster with an average of 8 subjects per cluster per time period (for a total sample size of 384 subjects) achieves 80% power to detect a difference between means of 0.56. The treatment mean is assumed to be 1.56 under the alternative hypothesis. The control mean is 1.00. The

standard deviation is 1.00. The test statistic used is the two-sided Wald Z-Test. The ICC is 0.010, and the significance level of the test is 0.050.

#### End of PASS Report

---

#### *Aim 4 Comparative Effectiveness Analyses*

##### *Aim 4 Analyses*

We will use standard step wedge analytic methods (see citations in reference list for PASS report). We will use repeated measures Poisson models to compare control vs LHS intervention conditions on the response rate ratio for the SU cascade outcomes and the opioid related outcomes. The Poisson or zero-inflated Poisson regression models will be performed using SAS GENMOD to fit repeated measures generalized linear models (GLIM) with generalized estimating equations (GEE) to account for the fact that event data for youth will be measured repeatedly over time and to account for the correlation due to within-organization clustering. The outcome data will be entered into the model as event counts for every 6-month period of the 36 months of implementation (6 months of control condition for all clusters, then 30 months of intervention), reported separately for each arrest record. Multiple arrests for the same youth will be used in the model. In the power analysis (described below), we conservatively based the power calculations on the number of unique youth arrested. The actual analysis will use a random effect to incorporate data from youth who have multiple arrests.

The amount of time (in days) exposed to the implementation for each adolescent arrestee will be accounted for in the rate ratio by defining the "offset" variable as the natural log of the number of days of exposure for every 6-month period of implementation. The primary denominator will be the number of arrested youth in the rolling intake cohort (e.g., % referred as a percentage of the number in the arrestee intake cohort). For some outcomes, another separate outcome will be derived and analyzed using a smaller denominator (e.g., % referred as a percentage of YJJ in need of treatment). The denominator for % in need (i.e., % screened positive) will be YJJ screened. The denominator for the % engaged will be the YJJ initiated. Because some youth will have multiple arrests, they could also have multiple screenings. In addition, for a single arrest and single screening, there could be multiple referral events over any 6-month period; for a single referral, there could be multiple treatment initiation events; and for a single treatment initiation, there could be multiple occurrences of an engaged event (i.e., 2+ behavioral health visits within 30 days after initiation) over any 6-month period. Therefore, the model will capture these multiple events as counts for every 6-month period.

Covariate-by-6-Month-Period interactions will be tested to determine whether the outcome response rates changed differently over time for different values of covariates.

In addition, youth-level covariates (demographics and health visit data) will also be included as predictors.

In the next step of the model, we will include organizational-level (i.e., county-by-system [JJ and CMHC]) survey predictors including staff characteristics (JPO age, sex, and race/ethnicity, time in current position, highest/type degree, number of previous positions, salary, caseload size, job (dis)satisfaction rating, turnover intentions, and burnout rating), implementation variables (readiness,

climate support, leadership support, and collaborative alliance), and fidelity variables (SIC Pre-implementation, Implementation score, and Sustainability scores; percentage of activities performed; and number of days between activities) to determine whether these survey variables predict the response rates for the SU cascade and opioid related outcomes. The implementation and fidelity measures will be entered as time-varying predictors because they will be available from multiple survey measurement time points as described above for the analysis of Aim 3.

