*Substance use care cascade.* A primary outcome of interest is the SU care cascade (Cascade). The Cascade includes a spectrum of outcomes. At any point in the Cascade, a young person can “drop out.” The earliest stage of the Cascade occurs within the juvenile justice system: identification of treatment need (i.e., screening and assessment) and referral to services. The latter end of the Cascade occurs within the CMHC: treatment initiation, engagement, and completion. We are interested in determining whether the LHS intervention is effective in improving the Cascade. We will evaluate this outcome utilizing administrative data on the entire population of YJJ across all 8 sites. We will gather Cascade data from the local CMHCs as well as Department of Child Services (DCS) and Medicaid. The reason for gathering data from DCS and Medicaid is they both provide funds for outpatient services. Thus, if a young person receives substance use services outside of the local CMHC, we will be able to gather at least a portion of it from these data sources. We may find that the effectiveness of LHS is improved for young people seeking services outside of the CMHC. With that said, we have collaborated with the largest CMHC of each jurisdiction and most jurisdictions only have one CMHC located in their county. We will also be able to control for time spent outside of the community by controlling for commitments to Department of Corrections (gathered from the juvenile justice data set) and residential placement (gathered from DCS and Medicaid).

*Criminal recidivism.* We will also assess whether the LHS intervention is effective in limiting recidivism. We will utilize the existing juvenile justice information system to assess recidivism. We will focus on the prediction of new criminal charges rather than charges associated with previous criminal behavior (e.g., technical violation, probation violation and warrants).

*Opioid-related outcomes.* By linking with data collected through the Regenstrief Institute Addictions Data Commons, we will be able to assess a variety of outcomes. This includes hospital and Emergency Department visits for opioid use disorders (OUD) as well as emergency medical service runs due to opioid use. These data elements are now incorporated within the Addiction Data Commons.

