|---------|----------------------------|-----------------------------------------------------------------------------|-------------------------------------------------------------------------------------------------------------------------------------------------------------------------------------------------------------------------------------------------------------------------------|
|         |                            | admin sample;
42 months LHS
intervention
sample                    | the LHS intervention on the Cascade (i.e., substance use treatment need identification, referral to services, initiation of services, and engagement in services).                                                                                                            |
| Primary | Criminal
recidivism     | 10 years, total
admin sample;
42 months LHS
intervention
sample | We will evaluate criminal recidivism across the 10-year administrative data collection period. We will assess if Cascade improvement is associated with decreased criminal recidivism. We will also assess if there are intervention-specific effects on criminal recidivism. |
| Primary | Opioid-related
outcomes | 10 years, total
admin sample;
42 months LHS
intervention
sample | We will use administrative data to assess opioid-related outcomes. We will assess if Cascade improvement is associated with decreased opioid-related outcomes. We will also assess if there are intervention-specific effects on opioid-related outcomes.                     |

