For the PASS input parameters, we assumed an intra-class (i.e., intra-cluster) correlation coefficient of 0.01, a two-sided test of the rate ratio (intervention vs control conditions), and an alpha of 0.05. We calculated power for 4 different hypothesized poisson rate ratios (effect size) ranging from 1.25 to 1.40 by .05. Results show that a total sample size of 2,400 youth (i.e., average of 300 unique youth per cluster with an average of 50 youth per cluster per 6-month time period) will provide 80% to 99% power for detecting population rate ratios, for various outcomes derived from administrative data described elsewhere, ranging from 1.25 to 1.40 (See PASS Report below). Thus, the available total sample size of 3,190 unique youth (i.e., average of 398 unique youth per cluster with an average of 66 youth per cluster per 6-month time period) will provide more than ample power (e.g., exceeding 80% power for a rate ratio of 1.25). In addition, the actual analysis will include youth with multiple arrests which will increase power further.

#### PASS Results Report for Power for Comparing Poisson Rates for Aim 4

Design Type: Incomplete (Custom)

Test Statistic: Wald Z-Test

Hypotheses:  $H_0: \lambda_1/\lambda_2 = 1$  vs.  $H_1: \lambda_1/\lambda_2 \neq 1$

|       | Design | Clusters | Cluster Size | Sample Size | Trt Rate    | Ctrl Rate   | Ratio | ICC   | Alpha |
|-------|--------|----------|--------------|-------------|-------------|-------------|-------|-------|-------|
| Power | S/T/R  | K        | M/m          | N           | $\lambda_1$ | $\lambda_2$ | RR1   |       |       |
| 0.80  | 5/6/1  | 8        | 300/50       | 2400        | 1.25        | 1.00        | 1.25  | 0.010 | 0.050 |
| 0.91  | 5/6/1  | 8        | 300/50       | 2400        | 1.30        | 1.00        | 1.30  | 0.010 | 0.050 |
| 0.97  | 5/6/1  | 8        | 300/50       | 2400        | 1.35        | 1.00        | 1.35  | 0.010 | 0.050 |
| 0.99  | 5/6/1  | 8        | 300/50       | 2400        | 1.40        | 1.00        | 1.40  | 0.010 | 0.050 |

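### Criminal recidivism is a Primary outcome, but the Aim 4 model text leaves it out and the general power statement does not fit its event rate

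*Protocol*

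**What the plan says.** The Outcome Measures table has the row "Primary | Criminal recidivism" and adds: "We will also assess if there are intervention-specific effects on criminal recidivism". The Assessing Outcomes section gives the expected direction: "We will also assess whether the LHS intervention is effective in limiting recidivism". It also defines the event as new criminal charges, leaving out technical violations, probation violations and warrants. The Synopsis names recidivism under Aim 4.

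The Aim 4 Analyses section describes a repeated-measures Poisson model that compares control and intervention on the "response rate ratio for the SU cascade outcomes and the opioid related outcomes". Its second step asks whether survey and fidelity measures "predict the response rates for the SU cascade and opioid related outcomes". Recidivism is in neither list, and the denominators given there are for Cascade steps. Event counts are entered per 6-month period, "reported separately for each arrest record. Multiple arrests for the same youth will be used in the model".

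The Aim 4 Power section states its result "for various outcomes derived from administrative data described elsewhere". The inputs are a control rate of 1.00, rate ratios of 1.25 to 1.40, an ICC of 0.01 and a two-sided alpha of 0.05. It concludes that 3,190 youth give more than enough power, above 80% at a ratio of 1.25. A recidivism figure appears once, "Based on an annual 30% recidivism rate", and serves only to reduce 4,557 arrests to 3,190 unique youth.

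**The concern.** Two parts of the protocol do not fit together.

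First, the Aim 4 text fixes software, record unit, offset, denominators and predictors, and names its outcomes twice. Both times it leaves out an outcome that the protocol calls Primary and intends to test. A later analysis plan could normally be left to fill in detail, but here the protocol has set out a model and excluded one of its own Primary outcomes from it.

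Second, the power statement names no outcome, so a reader will apply it to recidivism as well. Its control rate of 1.00 is five to seven times what the protocol's own 30% a year implies per 6 months. At stake is the reading of a null result on recidivism: it would be set against a power claim that was never shown for that outcome.

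**Working it through.** **Inputs (Aim 4 Power and its PASS report).** There are I = 8 counties and T = 6 periods of 6 months. Three counties start in period 2, three in period 3 and two in period 4. The ICC is 0.01 and alpha is 0.05, two-sided. The PASS run uses m = 50 youth per county-period; 3,190 youth give m = 66.

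**Formula.** Hussey-Hughes variance for a cross-sectional stepped wedge, with λ the mean of the two rates, σ² = 0.99λ/m and τ² = 0.01λ:

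Var = Iσ²(σ² + Tτ²) / [(IU − W)σ² + (U² + ITU − TW − IV)τ²]

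From the design matrix:
- U = 3×5 + 3×4 + 2×3 = 33
- W = 3² + 6² + 3×8² = 237
- V = 3×25 + 3×16 + 2×9 = 141
- IU − W = 264 − 237 = 27
- U² + ITU − TW − IV = 1,089 + 1,584 − 1,422 − 1,128 = 123

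**Reproducing the protocol (rate 1.00, ratio 1.25, m = 50).**
- λ = 1.125, σ² = 0.022275, τ² = 0.01125
- Var = 8×0.022275×0.089775 / (0.6014 + 1.3838) = 0.00806, SE = 0.0898
- z = 0.25/0.0898 = 2.785; power = Φ(2.785 − 1.960) = 0.795

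The four ratios give 0.795, 0.911, 0.968 and 0.991, against the stated 0.80, 0.91, 0.97 and 0.99. The method matches.

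**Recidivism rate per 6 months.** The protocol gives 30% a year. Half of that is 0.15. A constant hazard gives −ln(0.7)/2 = 0.178. The PASS report does not define its time unit; I assume the 6-month period.

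**Worked case (rate 0.178, ratio 0.80, m = 66).**
- λ = 0.1605, σ² = 0.99×0.1605/66 = 0.00241, τ² = 0.001605
- Var = 8×0.00241×(0.00241 + 6×0.001605) / (27×0.00241 + 123×0.001605) = 0.000884, SE = 0.0297
- Difference 0.0357; z = 1.20; power = Φ(−0.76) = 0.22

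**Results at m = 66.** For the follow-up rows, m is 66 times the period number, with the same covariance and generalised least squares.

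| Control rate per period | Follow-up | RR 0.80 | RR 1.25 |
|---|---|---|---|
| 1.00 (as assumed) | new intake only | 81% | 89% |
| 0.15-0.178 | new intake only | 20-22% | 23-27% |
| 0.15-0.178 | all later periods, no loss | 42-48% | 50-57% |
| 0.30 (read as per period) | new intake only | 34% | 41% |
| 0.30 | all later periods, no loss | 70% | 79% |

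The first row shows that the event rate, not the direction of the effect, drives the shortfall. At 0.15-0.178 with new intake only, an ICC from 0.001 to 0.05 keeps power between 19% and 30% over both ratios, and 80% power needs a reduction to a ratio of about 0.53-0.56.

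**The case against.** **Follow-up.** The strongest objection is that the cross-sectional run understates power. The protocol says after its PASS report that the design is mainly a cohort and that the run is conservative. This stands in part: repeated follow-up roughly doubles the power, which is why a range is needed and why 22% must not be read as a figure from the protocol. It does not rescue the claim within the 36 months on which the power statement rests. Five years of baseline with new intake only gives 21-29%. Carrying every youth forward from those five years with no loss does exceed 95%, but that contradicts the protocol's own allowance for 30% placed out of home or moving away.

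**Target effect.** The protocol states no reduction target for recidivism. The ratio of 0.80 is my choice, the reciprocal of the protocol's 1.25. A larger effect is easier to detect: at a ratio of 0.70, full follow-up gives about 77-84%.

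**Scope.** It would be too strong to say that power ignores recidivism. The general statement covers it by implication; what is missing is a rate that fits.

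**Double counting.** A reader might infer that rearrests will be counted more than once and that the result will be biased. The documents do not support this. They never say that recidivism enters by arrest record. If it did, a third arrest would be an event on the first and second records, but the records multiply too. With a 0.3 chance of each further arrest, record-level events are 3,190×0.3/0.7² = 1,953 over 4,557 records, and youth-level events are 1,367 over 3,190 youth. Both rates are 0.429. No bias in the rate ratio has been shown.

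**Conclusion.** The point holds in two parts. The omission is an inconsistency within the protocol and needs no assumption: a Primary outcome with a planned test is missing from both lists of outcomes in the Aim 4 model. The power statement is not supported for recidivism. At the protocol's 30% a year, power for a ratio of 0.80 or 1.25 is about 20-27% in the protocol's own framework and about 42-57% with complete follow-up over the 36 months. Even the most favourable combination within that period, 0.30 per period plus full follow-up, gives 70-79% and does not reach 80%.

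These figures assume equal counties, an ICC of 0.01, a 6-month time unit and a constant rearrest rate. They do not show that the trial cannot detect an effect on recidivism, since a larger reduction or much longer follow-up would raise power.

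**What to change.** 1. Name recidivism in the Aim 4 model. Define an index arrest, count new-charge arrests after it once per youth per 6-month period, and use days at risk as the offset. This keeps the same rearrest from appearing on several records, as it would if the arrest-record layout were extended to this outcome.
2. Limit the ample-power statement to outcomes that have the assumed control rate, and state the time unit of that rate.
3. Add a power line for recidivism: a reduction, a control rate derived from 30% a year, and the follow-up assumption stated.

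The cost is protocol wording and one further power calculation, with no change to design or data collection. The downside is that the stated power for this outcome becomes less favourable.
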